### Statistical Analysis

Data analyses will be performed using the R software (R Core Team, 2014), and lme4 package (Bates et al., 2015). First, preliminary analyses will be performed to test the assumptions of parametric statistics: if (strong) violations are detected, robust methods or data transformation will be applied. The EDE-Q 6.0 will be examined with the intention-to treat (ITT) analyses approach, with missing data replaced by baseline observations carried forward (BOCF) or last observation carried forward (LOCF), assuming no improvement for non-responders, as reported in previous studies (Castelnuovo et al., 2011). Dropouts will be excluded from the study.

The independent samples *t*-test will be used to examine between-group differences (BN *vs*. BED) in the EDE-Q 6.0 variables at all time-points, with attention to changes in the scores. The chi-square statistic will be used to test the association between treatment groups and socio-demographic variables (gender, age, marital status and employment status), and correlation analysis will be used to test the association between quantitative variables. Finally, multilevel growth curve model analysis will be used to estimate the average growth trajectories from baseline to one year after treatment for the EDE-Q 6.0 scores with corrected effect sizes (Hedges’ *g*) and 95% confidence interval.

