### Procedure

The study was approved by the research ethics committee of the clinic. Screening for inclusion will be conducted for consecutive patients at admission to the clinic by a clinical psychologist and psychotherapist who will be involved in the study screening and data collection stages only. Patients who will be eligible to participate will be subsequently informed about the study and invited to take part in the study. After completing the pre-treatment assessment (baseline), patients will receive 45–50 min of BST face-to-face treatment every 2 weeks for BN or BED based on their diagnosis for an anticipated total of 8 to 10 sessions. Participants will be assessed using the outcome measure (EDE-Q) at pre-treatment (T1), post-treatment (T2; approximately 16–20 weeks after the pre-treatment assessment), 6-month follow-up (T3), and 1-year follow-up (T4). During the treatment stage (T1 and T2), assessment will be conducted in a dedicated room at the clinic, whereas follow-up assessment (T3 and T4) will be conducted online.

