## Discussion

This paper provides a description of a proposal to evaluate the long-term efficacy of BST for the treatment of BN and BED in a real-world setting. Whilst the superiority of BST over CBT for the long-term treatment of BED has been shown in a previous study (Jackson et al., 2018), no research has yet investigated the long-term efficacy of BST for the treatment of BN. It is expected that findings will increase knowledge of the impact of BST for BED, while – for the first time – statistically testing the long-term effects of the BST protocol for BN. Due to its novelty, no hypothesis was made about the possible contribution of BST for the treatment of BN. Instead, it has been hypothesized that BST will promote sustained remission of BED symptoms.

Despite a few limitations – including the absence of a control group and the use of a single psychological measure – the research design is adapted to the clinical setting with the aim to move research into practice. Therefore, research findings will lack of generalizability, but will be useful to generate new formal hypotheses and to develop more precise research design in real-world settings.

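### Missing EDE-Q scores are to be filled by BOCF or LOCF with no rule for which, a rationale that fits only BOCF, and a dropout exclusion that contradicts the stated ITT approach

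*Protocol article*

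**What the plan says.** The Statistical Analysis section of the protocol article makes four statements that bear on missing scores:

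- Analysis set: "The EDE-Q 6.0 will be examined with the intention-to treat (ITT) analyses approach".
- Missing values: "missing data replaced by baseline observations carried forward (BOCF) or last observation carried forward (LOCF), assuming no improvement for non-responders". An earlier study is cited as precedent. Nothing says which method applies to whom, or which is primary.
- The sentence after that: "Dropouts will be excluded from the study".
- Main longitudinal analysis, in lme4: "multilevel growth curve model analysis will be used to estimate the average growth trajectories from baseline to one year after treatment", reported with Hedges' g and a 95% confidence interval.

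Under Procedure, the EDE-Q is taken at T1 (pre-treatment), T2 (post-treatment), T3 (six months) and T4 (one year). T1 and T2 take place at the clinic, while "follow-up assessment (T3 and T4) will be conducted online". Study Aim makes efficacy through one year the purpose of the study, and for BED the Discussion adds that "it has been hypothesized that BST will promote sustained remission of BED symptoms".

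**The concern.** Three things do not fit together.

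1. **Two rules, one rationale.** BOCF sets the change from baseline to zero, so it does assume no improvement. LOCF does so only when baseline is the sole score. Once a T2 or T3 score exists, LOCF holds the patient at that score. For someone last seen at T2, BOCF imposes full return to baseline at one year and LOCF imposes full maintenance.
2. **No selection rule.** As written, either method could be chosen after the scores are seen.
3. **Exclusion against ITT.** A patient cannot be kept in with filled-in scores under ITT and also be excluded as a dropout.

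At stake is the one-year result. The study has no control group, so change over time within patients carries the efficacy claim, and how patients lost after T2 are handled feeds directly into it. Both methods also pass copied values to the model as if they had been observed, so the standard errors and the Hedges' g interval do not reflect the missing information.

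**Working it through.** **The plan's own figure.** The only related calculation is the power of the group-by-time interaction. With partial eta squared 0.020, f = sqrt(0.020/0.980) = 0.1429. With N = 56, m = 4 and correlation 0.60, lambda = f² × N × m/(1 - 0.60) = 0.02041 × 56 × 4/0.40 = 11.43, on 3 and 162 degrees of freedom. Power is 0.810, which matches the stated figure and is not in dispute. The documents give no expected EDE-Q means, no relapse pattern and no missing-data rate, so every figure below is an assumption.

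**Step 1: what separates the two methods.** For a patient with a missing T4 score, BOCF gives a change of 0 and LOCF gives the change at the last observed visit. So:

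gap between LOCF and BOCF in mean T1-T4 change = sum over patterns of (fraction missing × gain at last observed visit).

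A patient with a baseline score only contributes nothing, because the methods then coincide.

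**Step 2: simplest case.** Assume a gain of 1 SD at T2, kept by completers, and 30% lost after T2. LOCF gives -1.0 SD and BOCF gives -0.7 SD. The truth is -1.0, -0.85 or -0.7 if those lost keep all, half or none of the gain. At 10, 20, 30 and 40% lost, LOCF stays at -1.0 while BOCF gives -0.9, -0.8, -0.7 and -0.6.

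**Step 3: illustration on the EDE-Q scale.** Assumed means are 4.0, 2.5, 2.8 and 3.1 at T1 to T4. At 30% missing at T4, half of these are also missing at T3, and missingness is unrelated to scores (completely at random).

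- Truth: 3.1 - 4.0 = -0.90.
- LOCF T4 mean: 0.70 × 3.1 + 0.15 × 2.8 + 0.15 × 2.5 = 2.965; change -1.035.
- BOCF T4 mean: 0.70 × 3.1 + 0.30 × 4.0 = 3.37; change -0.63.
- Gap by the Step 1 formula: 0.15 × 1.2 + 0.15 × 1.5 = 0.405, equal to 1.035 - 0.63.

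The same arithmetic over a range of missingness:

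| Missing at T4 | T1-T4 LOCF | T1-T4 BOCF | Truth | T2-T4 LOCF | T2-T4 BOCF | Truth |
|---|---|---|---|---|---|---|
| 20% | -0.99 | -0.72 | -0.90 | +0.51 | +0.78 | +0.60 |
| 30% | -1.035 | -0.63 | -0.90 | +0.465 | +0.87 | +0.60 |
| 40% | -1.08 | -0.54 | -0.90 | +0.42 | +0.96 | +0.60 |

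BOCF understates the change from baseline but overstates the T2-T4 relapse.

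**Step 4: loss that depends on the observed T2 score.** This simulation used 150 runs per row, N = 56, SD 1, correlation 0.6 and a T2 gain of 1 SD. Patients with worse T2 scores were more likely to be lost after T2 (missing at random). The model was a random-intercept mixed model with categorical time. Entries are mean T1-T4 change in SD units.

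| Relapse by T4 | Lost after T2 | Full data | LOCF | BOCF | Mixed model |
|---|---|---|---|---|---|
| none | 24% | -1.008 | -0.945 | -0.764 | -1.005 |
| none | 33% | -0.977 | -0.901 | -0.647 | -0.970 |
| half | 24% | -0.494 | -0.549 | -0.379 | -0.491 |
| half | 33% | -0.502 | -0.593 | -0.332 | -0.501 |
| full | 24% | -0.017 | -0.192 | -0.011 | -0.010 |
| full | 33% | -0.003 | -0.262 | -0.001 | -0.002 |

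LOCF is too favourable under half or full relapse and slightly conservative under none. The mixed model stays within 0.01 SD of the full-data value in every row.

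This has two limits. The fitted model matched the model that generated the data. Completers alone also came close to the full-data value (for example -0.497 against -0.502), because loss depended only on T2 and all correlations were equal. So the table shows that filling in creates bias. The wider advantage of the model rests on likelihood theory under missing at random, not on these runs. No standard errors were compared; that part is reasoning.

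**The case against.** **Overstatement.** A reader might infer that BOCF and LOCF give opposite answers, or that LOCF manufactures sustained benefit. The documents do not support either. In the illustration both methods show improvement from baseline (-1.035 and -0.63), and LOCF still shows relapse after T2 (+0.465 against +0.60). LOCF is too favourable only if those lost relapse, and the documents say nothing on that. This objection stands.

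**Reach of the filling-in.** If dropouts really are excluded, the rule touches only missed visits of patients who are retained, and the gap shrinks. That is true, but the plan then analyses a selected set while calling it ITT. The contradiction changes form and does not go away.

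**The powered contrast.** The sample size concerns the interaction of diagnosis with time. If loss and trajectories are similar in BN and BED, much of the bias cancels there. That is fair for that test. The stated aim, however, is change through one year, where nothing cancels.

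**Reading of the rationale.** The phrase could mean no further improvement. LOCF then fits, but BOCF does not, since it removes gain already observed. LOCF would still assume no relapse.

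**Left to an analysis plan.** A separate plan might choose between the methods. Choosing LOCF would still conflict with the rationale printed here, and the ITT conflict is in the article itself.

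**Importance.** The Discussion presents the study as hypothesis-generating and of limited generalizability. That limits the consequences but does not defend the rule.

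**Conclusion.** The point holds in this form: the filling-in rule is undefined, its rationale fits only BOCF once a post-baseline score exists, and the dropout exclusion contradicts ITT. The one-year change depends on the choice, by about the fraction missing times the gain at the last observed visit. Under the assumed means that is 0.27, 0.405 and 0.54 EDE-Q points at 20, 30 and 40% missing at T4.

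At 30%, LOCF overstates the true change by 0.135 (15% of 0.90) and BOCF understates it by 0.27 (30%). These sizes rest wholly on assumed means and missingness; the actual bias cannot be fixed from the documents. The direction of the LOCF error depends on what happens to those lost. The contradiction and the mismatch of rationale rest on the text alone.

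**What to change.** In the Statistical Analysis section:

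1. Make the primary analysis the planned lme4 multilevel growth model, fitted by maximum likelihood or REML to all observed EDE-Q scores of all enrolled patients, with no filled-in values. State that it is valid under missing at random if the model is correctly specified.
2. Delete the sentence that excludes dropouts. Without this the all-enrolled analysis would still contradict the text.
3. Remove LOCF.
4. Keep BOCF only as a named sensitivity analysis for change from baseline. Note that it is not conservative for the T2-T4 change (+0.87 against +0.60 in the 30% illustration), nor necessarily for BN against BED.

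The cost is wording only: the software and model are already planned. The downside is that the primary result relies on missing at random, which the data cannot confirm, so the sensitivity analysis is still needed. The change should be made before outcome data are seen.

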### Sample Size

The minimum sample size required to conduct this study was computed by using an *a priori sample size calculator* (G^∗^Power 3.1.9.2 software (Faul et al., 2007, 2009) for Fisher *f*’s tests. Participants – both BN than BED – will be measured with the EDE-Q 6.0 (Fairburn et al., 2008) at four time points: (1) at admission to the clinic, (2) at discharge, (3) at 6-month follow-up, and (4) at one year follow-up. *Clinical diagnosis* (BN *vs.* BED) was classified as between-group variable, and *time* was classified as within-subject variable. The *a priori* statistics (partial η^2^ and correlation between measures) were derived by considering previous longitudinal studies using the EDE-Q 6.0 (Fairburn et al., 2008) as measure of the range and severity of eating disorders’ features. The *a priori* partial η^2^ was set to assume a value of 0.020 (Fairburn et al., 2009) – small effect size (Cohen, 1988; Eid et al., 2017) – that provides a Cohen’s *f* equal to 0.143. Moreover, the Type I error (α) rate was set at 0.05 (two-sided) and the Power (1 – β) was set at 0.80, according to general guidelines (Cohen, 1988). In line with previous studies, the *a priori* correlation between repeated measures was set at 0.60 (Bardone-Cone and Boyd, 2007; Rose et al., 2013). Finally, sphericity was assumed. Results showed that there is an almost 81% chance of correctly rejecting the null hypothesis of no significant effect of the interaction with 28 subjects per group for a total of 56 participants.

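### The plan promises an intention-to-treat analysis and in the next sentence excludes dropouts, an undefined group; applying the exclusion gives a set that is not intention-to-treat and may overstate improvement

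*Protocol article*

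**What the plan says.** The Statistical Analysis section of the protocol article names the population: "The EDE-Q 6.0 will be examined with the intention-to treat (ITT) analyses approach". Missing values are to be filled with baseline (BOCF) or last (LOCF) observations, "assuming no improvement for non-responders". The next sentence reads: "Dropouts will be excluded from the study".

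The article does not say whether a dropout is a patient who leaves therapy, one who misses a questionnaire, or both. It does not limit the exclusion to a particular analysis.

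The Sample Size section gives "28 subjects per group for a total of 56 participants" as the minimum needed for almost 81% power on the interaction between diagnosis (BN or BED) and time. No dropout rate, inflation or replacement is mentioned. Study Design and Discussion both acknowledge that there is no control group.

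**The concern.** Carrying values forward under intention-to-treat is a way of keeping patients who leave. The following sentence takes such patients out. A statistician handed this text could defend either analysis set, and the choice could be made after the data are seen.

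Two things are at stake.

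- **Estimate of improvement.** The study aim concerns improvement under BST from T1 to one year after treatment. With one treatment and no comparator, that is a within-patient change. There is no second arm in which similar losses could offset a selection effect. If those who leave improve less than those who stay, excluding them raises the mean change.
- **Power.** The sample size is the smallest that meets the target, so any analysed number below it falls short for the interaction test.

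**Working it through.** **1. The two rules side by side**

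| Reading of dropout | Who is analysed | Is it intention-to-treat? | Does carry-forward still have a role? |
|---|---|---|---|
| Any patient with missing scores | Complete cases only | No | No |
| Patient who leaves therapy before discharge | Treatment completers | No | Yes, for missed T3 or T4 questionnaires |
| Exclusion not applied | All enrolled patients | Yes | Yes |

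The intention-to-treat label is correct only in the row where the exclusion sentence is ignored.

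**2. Size of the effect on mean improvement**

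Let d be the share of patients who drop out and c the mean change from baseline among those who stay. I read the plan's no-improvement assumption as covering patients whose later scores are missing, so their change is 0. A patient who leaves before T2 has only a T1 score, so BOCF and LOCF give the same value.

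- Mean change with all patients kept and baseline carried forward: (1 − d) × c + d × 0 = (1 − d) × c
- Mean change with dropouts excluded: c
- Ratio: c / [(1 − d) × c] = 1/(1 − d)

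| Assumed d | 1/(1 − d) |
|---|---|
| 10% | 1/0.90 = 1.11 |
| 20% | 1/0.80 = 1.25 |
| 30% | 1/0.70 = 1.43 |

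The article gives no dropout rate, so these values of d are assumptions.

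**3. Power**

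Inputs from Sample Size: partial η² = 0.020 (f = 0.143), α = 0.05, correlation ρ = 0.60, sphericity assumed, m = 4 measurements, k = 2 groups. The test is the repeated-measures within-between interaction, using the noncentral F distribution:

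- f² = 0.02/0.98 = 0.0204
- λ = f² × N × m/(1 − ρ)
- df1 = (k − 1)(m − 1) = 3
- df2 = (N − k)(m − 1)

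The plan's own case, N = 56: λ = 0.0204 × 56 × 4/0.40 = 11.43, df2 = 54 × 3 = 162, power = 0.810. The stated figure reproduces, and 56 is the smallest even N that reaches 0.80.

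Now suppose exactly 56 are enrolled and dropouts are removed equally from both groups, in whole patients:

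| Analysed N | Lost per group | Assumed dropout | Power |
|---|---|---|---|
| 56 | 0 | none | 81% |
| 54 | 1 | 2/56 = 3.6% | 79% |
| 50 | 3 | 10% (28 × 0.90 = 25.2, so 25) | 76% |
| 44 | 6 | 20% (28 × 0.80 = 22.4, so 22) | 70% |
| 38 | 9 | 30% (28 × 0.70 = 19.6, so 19) | 62% |

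**The case against.** Several points on the other side are fair.

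- **Carry-forward need not be pointless.** A reader might infer that the exclusion empties the carry-forward rule of all content. The article does not support that. If dropout means leaving therapy, carry-forward still fills follow-up questionnaires missed by patients who finished treatment. This stands. The label is still wrong, because enrolled and treated patients are discarded.
- **The power loss is conditional.** A reader might infer that the study is underpowered as planned. The article calls 56 a minimum and does not say that enrolment stops there. A shortfall needs enrolment of exactly 56 and at least one loss per group. A dropout allowance may also sit in a fuller protocol.
- **The 81% is not power for improvement under BST.** It concerns whether BN and BED patients change differently over time. The power loss and the bias in mean change concern different quantities and should not be merged.
- **Dropout is not shown to be likely or informative here.** The Introduction says many patients fail to respond to or complete CBT. That is a different therapy, it mixes non-response with non-completion, and it singles out comorbid personality disorders, while this study excludes comorbid psychiatric disorders that could bias the results. The article also says nothing about why patients leave, so it cannot be claimed that they leave because therapy is failing.
- **The aims are modest.** The Discussion concedes limited generalizability and a hypothesis-generating purpose. That lowers the weight the result will carry, but does not settle which patients are analysed.

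**Conclusion.** The plan is wrong as written. Nothing elsewhere in the article reconciles the intention-to-treat statement with the exclusion, and on any reading of dropout that gives the exclusion effect, the analysis set is not intention-to-treat.

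The direction of the bias is towards benefit, provided dropouts improve less than completers. The article has no data on this, but its own imputation assumption implies it. Under that assumption the overstatement relative to BOCF is 11% to 43% across assumed dropout of 10% to 30%.

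The power point is secondary. The stated 81% is correct for 56 analysed patients and has almost no slack, since 54 gives 79.4%. Any larger fall depends on enrolling exactly 56 and on the assumed losses.

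**What to change.** In Statistical Analysis:

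1. Delete the sentence excluding dropouts.
2. State that every consented patient with a T1 EDE-Q is in the primary growth-curve analysis, fitted to all observed scores.
3. Name BOCF as a sensitivity analysis, in place of the open choice between BOCF and LOCF. It is useful because patients with only a T1 score tell the growth model little about change, and BOCF shows the result if they did not improve.
4. Define dropout, and report any completer analysis only as a labelled secondary.

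In Sample Size, restate the 81% as applying to 56 patients with complete data.

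Optionally, invite patients who stop therapy to the T3 and T4 questionnaires, which are already online. This would strengthen the data but is not needed to remove the contradiction, and it may need a procedural change in a study that already has ethics approval.

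The cost is a few sentences of text, slightly more analysis work and probably a less favourable estimate. No extra recruitment is required to resolve the contradiction.

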### Outcome Measure

The *Eating Disorder Examination Questionnaire 6.0* (EDE-Q 6.0) (Fairburn et al., 2008) will be used as a measure of eating disorder feature severity. The EDE-Q 6.0 is a 28-item self-report questionnaire based on the EDE interview (Fairburn and Beglin, 1994). The items assess the frequency of behaviors indicative of an eating disorder over a 28-day period. The test is scored on a 7-point scale from 0 to 6 and has four subscales (i.e., restraint; eating concern; shape concern and weight concern) as well as a global score. The EDE-Q 6.0 has generally demonstrated adequately reliability and validity for eating-related pathology and specific disordered eating behaviors (Mond et al., 2004).

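### Raw BN-versus-BED t-tests at each follow-up visit mix any baseline gap with any difference in change, and no error control is stated for the roughly 20 tests

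*Protocol article*

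**What the plan says.** The Statistical Analysis section compares BN with BED by independent-samples t-tests "in the EDE-Q 6.0 variables at all time-points, with attention to changes in the scores". The Outcome Measure section describes an instrument with "four subscales (i.e., restraint; eating concern; shape concern and weight concern) as well as a global score", so five scores. The Procedure and Sample Size sections give four assessments: pre-treatment (T1), post-treatment (T2), six months (T3) and one year (T4).

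The Study Design section states that the study is observational and not randomised; the two groups are defined by diagnosis. Trajectories from baseline to one year are to come from a multilevel growth curve model, which is the only analysis that the Abstract names.

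The Sample Size section treats diagnosis as the between-group factor and time as the within-subject factor, and powers their interaction. There "the Type I error (α) rate was set at 0.05 (two-sided"), and power "was set at 0.80, according to general guidelines". The article gives no significance level or adjustment for the per-visit t-tests, and it names no EDE-Q score or visit as primary.

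**The concern.** In a randomised trial, the expected baseline difference is zero, so a comparison at follow-up estimates a treatment effect. Here it is not zero by design. At each visit after T1, the expected BN-BED difference is the T1 gap plus the difference in mean change. A raw t-test at T2, T3 or T4 tests that sum. A persisting gap can make it significant when both groups improve equally, and a gap in the opposite direction can hide a real difference in change.

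The article itself gives reason to expect a gap. Its Introduction ties the self-worth of people with BN to shape and weight, and two of the four subscales measure shape concern and weight concern.

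The closing words of the t-test sentence, about attention to changes, define neither a change-score test nor a baseline adjustment. If they mean separate change-score tests, these add 5 × 3 = 15, for 35 in all.

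A second, smaller issue is the number of tests. About 20 nominal p-values sit beside the growth model, with nothing stated to say which ones carry weight.

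**Working it through.** **1. The plan's own figure.** Inputs from the Sample Size section: partial η² "was set to assume a value of 0.020"; Cohen's f "equal to 0.143"; the "correlation between repeated measures was set at 0.60"; sphericity; 28 per group, N = 56; m = 4 visits.
- f = √(0.02/0.98) = 0.1429
- λ = f²·N·m/(1 − ρ) = 0.1429² × 56 × 4/0.4 = 11.43
- df = 3 and (56 − 2) × 3 = 162
- Power from the noncentral F = 0.810 (0.811 with f rounded to 0.143)
- N = 54 gives 0.794, so 56 is the smallest even total that reaches 0.80.

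The stated figure of almost 81% is reproduced. It belongs to one test, the diagnosis-by-time interaction.

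**2. Number of t-tests.** 5 scores × 4 visits = 20, of which 5 are at baseline and 15 after it.

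**3. Baseline gap with identical change.** Assume a constant gap of d SD, equal variances and 28 per group. The raw t statistic at a follow-up visit is noncentral t with 54 df and noncentrality d·√(28/2) = d·√14. The chance for any of the three visits, and the change-score results, come from 20,000 simulated data sets with correlation 0.60 between visits. The documents give no gap, so a range is shown.

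| Assumed gap (SD) | Noncentrality | Raw t-test significant, per visit | Any of T2-T4 | Change-score test, per visit | Change-score test, any of three |
|---|---|---|---|---|---|
| 0.2 | 0.75 | 11% | 23% | 5% | 13% |
| 0.3 | 1.12 | 20% | 36% | 5% | 12% |
| 0.5 | 1.87 | 45% | 68% | 5% | 13% |
| 0.8 | 2.99 | 84% | 96% | 5% | 13% |

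The change-score test holds its level whatever the gap. At the plan's correlation of 0.60 and with equal variances, change has variance 2 × (1 − 0.6) = 0.8 of the raw-score variance, so it is also somewhat more precise.

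**4. No BN-BED difference at any visit.** Take each test at 0.05, which is an assumption because the article sets no level for these tests. The expected number of false positives is 20 × 0.05 = 1. If the 20 tests were independent, the chance of at least one would be 1 − 0.95²⁰ = 0.64. They are not independent: the scores are related and measured repeatedly on the same people. The simulation used correlation 0.60 over time, an assumed correlation between subscales, and the global score as the mean of the subscales (also an assumption).

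| Assumed correlation between subscales | At least one of 20 | At least one of the 15 after baseline |
|---|---|---|
| 0.3 | 45% | 39% |
| 0.5 | 41% | 35% |
| 0.7 | 35% | 29% |
| 0.8 | 30% | 25% |

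For the global score alone at four visits, the figure is about 14%.

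Steps 3 and 4 rest on different premises (a gap, and no gap). They describe alternative situations and must not be added together.

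**The case against.** The t-tests are not presented as the main analysis. They are listed with chi-square and correlation analyses ahead of the growth model, and the Discussion presents the results as a source of new hypotheses. The stated aim is improvement after therapy, not a contest between the two protocols. This is also a condensed article, and a fuller plan may set a multiplicity rule and a primary score. All of this stands. It limits the multiplicity part, which rests largely on silence, and 5 of the 20 tests are baseline descriptions in any case. It does not rescue the follow-up t-tests, because the article fixes those itself and a multiplicity correction would not change what they measure.

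Stronger readings are tempting, but the document does not support them:
- **A reader might infer that the alpha and power of the sample-size section fail.** They apply to the single interaction test, and side analyses leave its error rate unchanged.
- **A reader might take 64% from independence and conclude that a false positive is more likely than not.** With correlated tests the range is 30-45%.
- **A reader might infer that the investigators will read a persisting gap as one protocol working better.** The article does not say so. It calls the diagnostic groups treatment groups in one place, which leaves room for that reading, but no BN-versus-BED efficacy claim is planned.
- **A reader might infer that no adjustment will be made.** The article states none, which is not the same.

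**Conclusion.** The point holds for the analysis that the article fixes. Raw BN-BED t-tests at T2-T4 do not isolate a difference in change, do not test the effect on which the study is sized, and are not repaired by an undefined reference to changes. How far they mislead depends on the baseline gap, which the documents do not give: about 11% to 84% significant results per visit for gaps of 0.2 to 0.8 SD, with equal change, equal variances and 28 per group. The multiplicity part is secondary: about 30-45% for at least one nominal finding when no difference exists, for assumed between-subscale correlations of 0.8 down to 0.3. The sample-size calculation is correct and untouched. A change is worth making because the better analysis can come from a model that is already planned.

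**What to change.** Take the BN-BED comparison from diagnosis-by-time contrasts (difference in change from T1 to T2, T3 and T4) in the planned multilevel model. Preferably name one EDE-Q score, such as the global score, as primary; a single interaction test on that score keeps alpha at 0.05 and matches the powered effect. Drop the T2-T4 t-tests, or keep the visit means and label the comparisons descriptive. Keep T1 as a descriptive baseline comparison. Report the four subscales as secondary, with estimates and intervals. Replace the phrase about attention to changes with the contrast that is meant.

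The cost is a few sentences of plan wording. No extra patients, visits or data are needed. The downside is fewer nominal p-values to report.
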